In consonance with this idea, an impaired capacity to perform attention-demanding mobility activities such as carrying out two tasks (physical + cognitive) simultaneously, also known as *dual-task*, could be a novel marker of physical and cognitive frailty. Many activities of daily life involve the performance of several tasks at a time, creating competing demands for attentional resources that challenge both motor and cognitive functions [14]. Considering that attentional capacity is limited, when demands exceed capacity, performance of dual-tasks can be affected compared to performance of the same tasks in a *single-task* fashion. Indeed, older adults show greater impairments compared to their younger counterparts in cognitive-motor dual-task performance, such as naming animals while walking or making calculations during balance exercises [15, 16]. Additionally, low dual-task performance capacity is associated with cognitive impairment and with a high risk of falling [17–19].

Previous studies of dual-task as a test of functional performance in older adults have focused on the gait speed test or on the Timed Up and Go test as physical tasks, while introducing semantic fluency or a calculus command as cognitive content. The difference between performance in the dual-task and the single-task tests is known as *dual-task interference* or *dual-task cost* [20]; this difference increases with aging [21]. The dual-task cost can be accounted for in both the physical and the cognitive domains. In this regard, the most commonly used formula is: dual-task cost = ((dual task − single task) single-task) × 100% [18]. For the physical dual-task cost calculation, time in seconds is used, whereas for the cognitive dual-task cost, either the number of correct responses or the percent of correct responses can be used to compare between single and dual task performances.

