### Outcome measures

The primary outcome measure will be gait speed under dual-task conditions. The distance to be covered will be 9 m on a smooth non-slippery surface with starting and ending points marked on the floor with tape. The cognitive task to be performed will previously be explained to participants. Straight after the explanation, the participant will be asked to walk at a comfortable pace on a straight line while simultaneously performing the cognitive task. Time to perform the test will be measured following the procedure described by Bohannon [36]. Gait speed will be then calculated dividing the covered distance (in meters) by the employed time (in seconds).

In addition, both gait spatiotemporal parameters (cadence, single and double support time, etc.) and cognition (number of correct, incorrect and total responses) will be analyzed, and compared with performance in the single-task modality. This difference is referred to as dual-task cost, and will be calculated using the formula: ((dual task – single-task)/single-task × 100) [18].

Secondary outcome measures will include functional (Table 4), cognitive, and emotional assessments (Table 5). Functional capacity will be determined by the following tests (Table 4): the Short Physical Performance Battery test [37] (SPPB); the Senior Fitness Test [38] (SFT); the instrumented Timed Up and Go test [39] (iTUG; BTS Biomedical G-WALK triaxial accelerometer and gyroscope); usual walking speed [36]; the handgrip strength test [40] (Jamar dynamometer) and Berg balance test [41]. Frailty assessment will include the Tilburg Frailty index [42], the Frailty index [43] and the Rockwood clinical frailty scale [44]. In addition, participants will wear an accelerometer (Actigraph GT3X model (Actigraph LLC, Pensacola, FL, USA)) on the hip with a belt for 7 days to measure active and sedentary periods during everyday life, by daily step quantification. Active-period intensities will be classified as light, moderate or vigorous based on Freedson and colleagues’ criteria [45] and recorded in minutes.

**Table 4 Tab4:** Functional assessment tests

Test (Reference)	Functions/Parameters	Description
Short Physical Performance Battery (SPPB) (Guralnik et al., 1994)^a^	Lower extremity function: static balance, gait speed and getting in and out of a chair	Side-by-side, semi-tandem and tandem stands (10 s); 4 m walk test at comfortable speed and 5 quickly sit to stand from a chair without upper extremity assistance

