### Dual-task assessment

The secondary tasks included in the dual-task evaluation will be of three different natures: 1) semantic fluency: naming animals or fruits and vegetables; 2) backward counting by ones; and 3) inhibition ability through the Go no go test (when the evaluator says ‘one’, the participant has to respond ‘two’ and viceversa). We selected these tasks by the following process: a) a review of the literature, b) expert consultation through interviews and a discussion group, c) final selection.

Cognitive tasks will be applied during two different physical function tests: 9 m usual gait speed and the Timed Up and Go test. In addition, these physical tasks will be performed in a single task mode to allow for dual-task cost calculation. Dual-task gait speed and dual-task Timed Up and Go tests will be performed on two non-consecutive testing days to minimize learning effects and the order of the dual-task and the single-task will be randomized for the same purpose. In addition, participants will wear an accelerometer (BTS Biomedical G-WALK triaxial accelerometer and gyroscope) during the tests to measure gait kinematic parameters such as step number, cadence, step symmetry, and step time variability. The number of total responses, errors, repetitions, and stops will be recorded. No instructions will be given regarding task prioritization.

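### The percent dual-task cost is applied to the number of incorrect responses, a count that can be zero, so this one derived outcome is undefined for residents with no single-task errors and unstable for those with one or two.

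*Protocol article*

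**What the plan says.** The Outcome measures section lists, in addition to the primary outcome, "both gait spatiotemporal parameters (cadence, single and double support time, etc.) and cognition (number of correct, incorrect and total responses". These are to be analysed and set against single-task performance. The section continues: "This difference is referred to as dual-task cost, and will be calculated using the formula", and it gives one formula: "dual task – single-task)/single-task × 100". It does not exempt incorrect responses and does not say what happens when the single-task value is zero.

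The Dual-task assessment section names the cognitive tasks: semantic fluency, "backward counting by ones; and 3) inhibition ability through the Go no go test". On the data collected it says: "The number of total responses, errors, repetitions, and stops will be recorded". Errors are therefore non-negative whole numbers.

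The Introduction, describing common practice, is narrower. For cognitive cost it says that "either the number of correct responses or the percent of correct responses can be used to compare" single-task with dual-task performance, and it does not mention errors. For the physical side it says: "For the physical dual-task cost calculation, time in seconds is used".

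**The concern.** A percent change needs a denominator that stays away from zero. Error counts on tasks such as counting backward by ones do not guarantee that. A resident who makes no single-task errors has no error cost, whatever happens under dual task. A resident who makes one or two has a cost that swings by 50 or 100 percentage points for each further error.

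At 3 months, whether a resident has a value is settled after randomisation by single-task performance. The dual-task arm practises closely related skills: Table 3 includes inhibition by giving the opposite answer, forward and backward calculation, and semantic naming. The multicomponent arm does not. The two arms could therefore contribute differently selected residents to this comparison, although the Statistical considerations section calls for intention-to-treat analyses.

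**Working it through.** **Inputs.** The formula, the list of measures and the recording of errors as counts come from the Outcome measures and Dual-task assessment sections. The total of 188 participants comes from Power and sample size. The protocol gives no error rate, so the Poisson means below are assumptions, shown as a range. There is no figure in the protocol on this point to reproduce.

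**Step 1: the formula on small counts** (illustrative values).

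| Incorrect responses, single → dual | (dual − single)/single × 100 |
|---|---|
| 4 → 5 | (5 − 4)/4 × 100 = +25% |
| 1 → 2 | (2 − 1)/1 × 100 = +100% |
| 0 → 2 | 2/0, undefined |
| 0 → 0 | 0/0, undefined |

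The first two rows are the same deterioration, one extra error, and differ fourfold in cost.

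**Step 2: how many residents have no value at one visit, for one task.** If single-task errors are Poisson with mean λ, the share with none is exp(−λ).

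| Assumed λ | exp(−λ) | Of 188 |
|---|---|---|
| 0.25 | 78% | about 146 |
| 0.5 | 61% | about 114 |
| 1 | 37% | about 69 |
| 2 | 14% | about 25 |
| 3 | 5% | about 9 |

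The planned models may include the baseline measurement as a covariate, and then a value is needed at both visits. If the mean is the same at both visits and the counts are independent, the share lost is 1 − (1 − exp(−λ))²: 85%, 60% and 25% for λ = 0.5, 1 and 2. If the same residents make no errors each time, the shares stay at 61%, 37% and 14%.

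**Step 3: does the ratio still measure cost among those who keep a value?** Let S be single-task errors, Poisson with mean λ. Let D be dual-task errors with mean 1.5λ, independent of S. The true cost is then +50% at every error level. Among residents with S ≥ 1, the expected computed cost is

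(1.5λ × E[1/S given S ≥ 1] − 1) × 100.

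| λ | E[1/S given S ≥ 1] | Expected computed cost |
|---|---|---|
| 0.5 | 0.8789 | 1.5 × 0.5 × 0.8789 − 1 = −34% |
| 1 | 0.7670 | 1.5 × 1 × 0.7670 − 1 = +15% |
| 2 | 0.5766 | 1.5 × 2 × 0.5766 − 1 = +73% |

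One constant true cost of +50% appears as −34%, +15% or +73%, depending only on how many single-task errors are made. Two arms that differ in single-task errors but not in true cost would therefore differ on this outcome. Independence of S and D is an assumption. The table shows that distortion can be large; it does not predict its size in this trial.

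**Step 4: sign and scale of the other costs.** Under the one formula, deterioration is positive for time, double support time and incorrect responses, and negative for speed, cadence and correct responses. For the 9 m walk, a fall from 1.0 to 0.8 m/s lengthens the time from 9 to 11.25 s. On seconds the cost is (11.25 − 9)/9 × 100 = +25%; on speed it is (0.8 − 1.0)/1.0 × 100 = −20%.

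**The case against.** The strongest reply is that this is one derived, non-primary variable. No rule in the protocol excludes anyone. The raw counts of correct, incorrect and total responses are to be analysed in their own right, and handling a zero denominator is the kind of detail that a statistical analysis plan settles. The error rates above are assumed, and residents may be admitted with a MEC-35 score as low as 20, so zero errors may be less common than the simplicity of the tasks suggests.

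Most of this stands and limits the reach of the point. It does not remove it. The protocol does not leave the derivation open: it names incorrect responses and fixes the formula. A later plan that follows it inherits a ratio that cannot be computed for some residents. A convention for zero would not cure the instability at one or two errors.

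A reader might infer more, and three stronger readings are not supported.

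- *The comparison is biased against the better-trained arm because its best performers are lost.* The protocol gives no basis for a direction. A resident with no single-task errors can only stay level or worsen under dual task, so improved scores are not what is lost. Under the independence assumption in step 3, the arm with fewer errors would look better on error cost, not worse.
- *The differing signs undermine the results.* Reversing a sign leaves the between-arm test for a single outcome unchanged, and no composite or ranking of costs is planned.
- *The Introduction contradicts the Methods on seconds and speed.* The Introduction describes common practice. The Methods define speed for the primary outcome, which is not a cost, and the Timed Up and Go is naturally a time.

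**Conclusion.** The concern holds for the percent cost of incorrect responses. That the ratio is undefined at zero and unstable at one or two errors follows from the formula and needs no assumption. How many residents are affected does need one: 61%, 37% or 14% at a visit for assumed Poisson means of 0.5, 1 or 2, and 78% to 5% over means from 0.25 to 3. The arm comparison on this outcome may be distorted because having a value at 3 months depends on post-randomisation performance that one arm trains. The direction is not determined by the protocol.

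The affected residents would lack this one derived value. They remain in the trial and in every other outcome, and the primary outcome is untouched. The missing sign convention and the open choice between speed and seconds for the walking cost are minor wording matters.

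**What to change.** In Outcome measures, remove incorrect responses from the percent-cost formula. Analyse instead the dual-minus-single difference in the number of errors, or the difference in percent correct, in percentage points. Percent correct is already mentioned in the Introduction, but it may reach a ceiling on easy tasks and is undefined for a resident who gives no response, so a rule for that case is needed if it is chosen. Keep percent cost for measures whose single-task value cannot be zero.

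In the same section, state for each cost measure which sign means worse, and whether the 9 m walking cost is computed on speed or on seconds.

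The cost is wording and derivation code; no new data or assessments are needed. The one loss is that error counts are no longer reported as a percent cost, which makes them less directly comparable with the other costs.

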### Dual-task assessment

The secondary tasks included in the dual-task evaluation will be of three different natures: 1) semantic fluency: naming animals or fruits and vegetables; 2) backward counting by ones; and 3) inhibition ability through the Go no go test (when the evaluator says ‘one’, the participant has to respond ‘two’ and viceversa). We selected these tasks by the following process: a) a review of the literature, b) expert consultation through interviews and a discussion group, c) final selection.

Cognitive tasks will be applied during two different physical function tests: 9 m usual gait speed and the Timed Up and Go test. In addition, these physical tasks will be performed in a single task mode to allow for dual-task cost calculation. Dual-task gait speed and dual-task Timed Up and Go tests will be performed on two non-consecutive testing days to minimize learning effects and the order of the dual-task and the single-task will be randomized for the same purpose. In addition, participants will wear an accelerometer (BTS Biomedical G-WALK triaxial accelerometer and gyroscope) during the tests to measure gait kinematic parameters such as step number, cadence, step symmetry, and step time variability. The number of total responses, errors, repetitions, and stops will be recorded. No instructions will be given regarding task prioritization.

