## Methods

### Study design and participants

Based on the proposed objective, an experimental multicentre simple randomized study was designed (Aging-ON_DUAL-TASK_). Participants will be randomly allocated to either a multicomponent exercise program or to the same multicomponent program with simultaneous cognitive training (dual-task program). Participants will be recruited from eight long-term nursing homes in Gipuzkoa, Basque Country, Spain. Each site will enroll a minimum of 16 subjects and interventions will take place between June 2018 and December 2018. Researchers responsible for data gathering will be blinded to group assignment. The assessments will be carried out by research staff at baseline and at 3 months after the beginning of the intervention. The study has been designed and results will be reported following the CONSORT Statement extension for trials of non-pharmacological interventions and pragmatic intervention trials (Fig. 1).

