### Inclusion and exclusion criteria, recruitment, and randomization

The inclusion criteria, recruitment, and randomization methodologies in the Aging-ON_DUAL-TASK_ study will be the same as on a previously published protocol [33]. The inclusion criteria will be: age ≥ 70 years old; a Barthel Index [34] score ≥ 50 and score ≥ 20 on the MEC-35 Test [35] [Mini-examen cognoscitivo, an adapted and validated version of Mini Mental State Examination (MMSE) in Spanish]; and capacity to stand up and walk independently for at least 10 m. Participants will not be eligible if they are judged clinically unstable by the medical staff, or have in any other condition in which entering the study would not be in the subject’s best interests.

Identification of individuals that meet the inclusion criteria will be facilitated by the databases of the included long-term nursing homes. The primary recruitment strategy will be information provided to the potential participants by the medical and nursing professionals from each facility. All volunteers will receive detailed study information at their reference sites through the research team: objectives, measurement variables, and other details about the interventions will be explained orally and in writing to both potential participants and their families. After signing the informed consent, the participants within each center will randomly be assigned (in a 1:1 ratio) through sealed opaque envelopes to either the multicomponent or the dual-task group by coin-tossing sequence generation.

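### Inhibition scores that count responses to cues spoken live by the evaluator mix cue pace and walking time with inhibition ability

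*Protocol article*

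**What the plan says.** All references are to the Protocol article.

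- **Dual-task assessment.** "The secondary tasks included in the dual-task evaluation will be of three different natures": semantic fluency, backward counting by ones, and inhibition. The third is tested as "inhibition ability through the Go no go test (when the evaluator says" one, the resident replies two, and the reverse. In fluency and counting the resident produces answers at their own speed. In the inhibition task each answer waits for a spoken cue.
- **Dual-task assessment, on where the tasks are used.** "Cognitive tasks will be applied during two different physical function tests: 9 m usual gait speed and the Timed Up and Go test".
- **Outcome measures, on gait.** "The primary outcome measure will be gait speed under dual-task conditions". "Gait speed will be then calculated dividing the covered distance (in meters) by the employed time (in seconds"), over 9 m. The section does not say which of the three cognitive tasks defines this outcome.
- **Outcome measures, on cognition.** The "number of correct, incorrect and total responses" are analysed and compared with single-task performance. The cost is the dual-task value minus the single-task value, divided by the single-task value, times 100.
- **Study design and participants.** "Researchers responsible for data gathering will be blinded to group assignment".
- **Inclusion and exclusion criteria, recruitment, and randomization.** Before consent, "objectives, measurement variables, and other details about the interventions will be explained orally and in writing" to residents and families. Allocation is individual, 1:1, within each home.

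**The concern.** A response count measures ability only if every resident has the same opportunity to respond. Here the opportunity varies for two reasons unrelated to inhibition: how quickly the evaluator speaks, and how long the resident takes to walk 9 m. The second is awkward for this trial, because a shorter walking time is what the intervention is meant to produce. A resident who walks faster at 3 months and is just as accurate would give fewer correct answers, and the count-based cost would show this as cognitive loss. The cognitive side of dual-task performance could then be misread, and an apparent trade-off between gait and cognition could be an artefact of scoring.

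There is a smaller issue on the gait side. If cue pace alters how demanding the walk is, uneven live pacing adds variation to gait speed in the inhibition walk.

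**Working it through.** The plan gives no figure for cue pace or number of cues, so there is none to reproduce. The check asks what count scoring does.

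**Inputs**
- From the Protocol article: distance 9 m (Outcome measures); target difference 0.08 m/s (Power and sample size); the cost formula (Outcome measures).
- Assumed: walking speed 0.70 m/s, with a range of 0.50 to 0.80 m/s; cue interval 1.5 s or 3 s.

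**Step 1. What a count contains.** Let v be walking speed, d the cue interval, and p the proportion of cues answered correctly. Walking time is T = 9/v, the number of cues is about T/d, and the number of correct answers is C = p × T/d. Only p concerns inhibition.

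**Step 2. Effect of pace.**

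| Speed (m/s) | Walk (s) | Cues at 1.5 s | Cues at 3 s |
|---|---|---|---|
| 0.50 | 18.0 | 12.0 | 6.0 |
| 0.70 | 12.9 | 8.6 | 4.3 |
| 0.80 | 11.3 | 7.5 | 3.8 |

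In whole cues at 0.70 m/s this is 8 against 4. Doubling the interval halves the attainable count at every speed.

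**Step 3. Effect of walking speed at a fixed pace.** Going from 0.70 to 0.78 m/s shortens the walk from 9/0.70 = 12.86 s to 9/0.78 = 11.54 s. The ratio of cues is 11.54/12.86 = 0.70/0.78 = 0.897, or 10.3% fewer, whatever the interval. From 0.50 to 0.58 m/s the loss is 1 − 0.50/0.58 = 13.8%. From 0.80 to 0.88 m/s it is 1 − 0.80/0.88 = 9.1%.

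**Step 4. Effect on the cost.** With subscripts D for dual task and S for single task, the count-based cost is

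[(p_D/p_S) × (T_D/T_S) × (d_S/d_D) − 1] × 100.

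Hold accuracy equal (p_D = p_S). For illustration, let the single-task test also last 12.86 s; its length is not given in the article.
- Same pace, walking at 0.70 m/s: cost 0%.
- Same pace, walking at 0.78 m/s: (0.897 − 1) × 100 = −10.3%.
- Walking at 0.70 m/s, cues every 3 s in dual task and every 1.5 s in single task: (0.5 − 1) × 100 = −50%.

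None of these differences reflects inhibition. The factor of 0.897 does not depend on the assumed single-task length, provided that length is the same at both visits.

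**Step 5. The alternative score.** Percentage correct of cues presented is 100 × p. Its cost is (p_D/p_S − 1) × 100, which is 0% in all three cases. Pace could still change p, since faster cues may be harder, so the interval has to be fixed as well.

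**Step 6. Gait speed.** The documents contain no figure linking cue pace to gait speed, so the added noise in the inhibition walk cannot be sized.

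**The case against.** **The cue rate may be specified elsewhere.** A cue interval, script or evaluator training can sit in the full protocol or a testing manual, and an article may leave them out. The article does not say that cues are freely paced. This stands: an unstated rate is not the error. It does not rescue the count, because Step 3 applies even when the pace is perfectly constant.

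**Percentages are available, and duration affects the other tasks too.** The Introduction accepts either a count or a percentage for the cognitive cost. Since correct, incorrect and total responses are recorded, percentage correct of responses given could be computed. That stands, so the data are not useless. But Outcome measures names the counts as what is analysed, and a percentage of responses given ignores cues left unanswered. Fluency and counting totals also depend on walking time, but they have no evaluator pace in them.

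**A reader might infer that the assessor sets the load on the primary outcome and that blinding gives no protection.** The documents do not support this.
- The inhibition walk is one of three, and the article does not say that it defines the primary outcome.
- Assessor blinding is stated, and it protects while it holds. Residents who know their programme could reveal it, but that is true of most assessor-blinded exercise trials, and nothing shows that it happens here.
- Allocation is individual and 1:1 within homes, so pace differences between evaluators, homes or visits that are unrelated to arm give noise, not bias.
- Bias would need pacing that depends on arm. One route is a lost blind. Another is an evaluator who waits for each answer, so that residents practised in similar reversal tasks (Table 3, Inhibition row) receive denser cues. Both are conjecture.

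**Conclusion.** The point holds for the cognitive score. As written, the number of responses in the inhibition task, and the dual-task cost built on it, mix evaluator pace and walking time with inhibition ability. The distortion from walking time alone is about 10% for the targeted 0.08 m/s gain at an assumed 0.70 m/s, and 9% to 14% for starting speeds of 0.80 down to 0.50 m/s. The distortion from pace is proportional: half the pace gives half the count. The speeds and cue intervals are assumptions; the proportional relations follow from the 9 m distance and the cost formula.

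For gait speed the conclusion is weaker. Variable live cueing may add noise to the inhibition walk, by an amount the documents do not allow one to estimate. It matters for the primary outcome only if that walk is, or contributes to, it. A systematic difference between arms is not shown.

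**What to change.** - **Dual-task assessment:** deliver the one/two cues from a recorded sequence at a single fixed interval, the same for every resident, home and visit, and for single-task and dual-task performance.
- **Outcome measures:** score inhibition, and its dual-task cost, as the percentage correct of cues presented, not the number of responses. Both changes are needed: the fixed interval equalises the pace, and the percentage removes the dependence on walking time.

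The cost is an audio file and a device to play it, with no extra staff, visits or residents. There are two downsides. A fixed pace cannot adapt to slow responders, whose omissions count as errors. The percentage is also coarse on a short walk: one cue is worth 12.5 percentage points with 8 cues and 25 with 4, which should be weighed when the interval is chosen.

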Dual-task performance can be modified with specific dual-task training [22, 23]. In fact, this type of intervention can maintain or even improve cognitive function [24, 25], especially executive function [26]. Two models have been suggested that might explain training-mediated dual-task performance changes [27]. The task-automatization model is based on the assumption that individual tasks can be automatized and predicts similar improvements either with single-task or dual-task training [27]. Alternatively, the task-integration model advocates for the efficient integration of both tasks through dual-task training, resulting in dual-task performance improvements [27]. According to the latter model, dual-task performance would only improve after dual-task but not single-task training. Furthermore, dual-task training may be superior to single-task training [28–30], since dual-task training requires greater cognitive and motor resources and is more complex in terms of control and coordination demands. Pellecchia et al. [31] observed greater improvements in postural sway under dual-task conditions after dual-task training compared to single-task training, supporting the task-integration model and suggesting that both physical and cognitive functions interact in a way still to be revealed.

To our knowledge, no studies have explored the effects of a supervised dual-task multicomponent exercise intervention in long-term nursing home facilities from a broad perspective of frailty, assessing functional capacity under single-task and dual-task conditions, physical activity, cognitive performance and emotional status. Therefore, we designed a randomized multicenter study, the Aging-ON_DUAL-TASK_ study, to test hypothesis that the addition of cognitive training to a supervised multicomponent exercise program can improve gait speed performance under dual-task conditions by, at least 0.08 m/seg in a population of older adults in long-term nursing homes. The major aim of the Aging-ON_DUAL-TASK_ study is to determine if a supervised dual-task program carried out in long-term nursing homes can attenuate frailty to a greater extent than the same multicomponent exercise program without cognitive training.

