## Discussion

The current trial is a large multi-center randomized study aiming to investigate whether dual-task performance, including gait and cognitive parameters, can be improved by specific dual-task training. So far, guidelines for the geriatric population and professionals working in the field are scarce, despite the exponentially increasing number of people above 65 years old. Older adults in long-term nursing homes are at particular risk of adverse outcomes and have been the focus of interventions aiming to prevent or reverse frailty [55].

The results of the present study will add valuable knowledge about the effects of the dual-task program in long-term nursing home residents, taking together functional, cognitive, and emotional variables linked to frailty. Particularly, analysis of a multicomponent exercise program and the same program with simultaneous cognitive training, or dual-task, will help us to design interventions to improve or at least maintain functionality and cognition in long-term nursing home residents.

One of our main concerns at the time of designing the dual-task intervention was the fact that when performing a dual-task exercise, the execution velocity of the physical task could be reduced when compared with a single task exercise. In addition, movement technique could also be altered if compared to single task training. Consequently, we feared that a dual-task program might affect physical performance and hence not improve physical parameters to the same extent as the multicomponent program. Thus, we conducted a pilot study to ascertain if both the multicomponent and the dual-task programs produce similar training adaptations, in which we successfully observed significant physical improvements in both groups [56].

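### Dual-task gait speed tests the stated hypothesis but cannot by itself show better overall dual-task performance, and response counts on a fixed 9 m walk do not cleanly reveal a trade-off

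*Protocol article*

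**What the plan says.** The Outcome measures section states: "The primary outcome measure will be gait speed under dual-task conditions". Speed is 9 m divided by the time taken, and no cognitive response enters the score. The participant has the cognitive task explained and is then asked to do it while walking at a comfortable pace. The Dual-task assessment section adds: "No instructions will be given regarding task prioritization".

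Cognitive performance on these tests is not ignored. The same section says: "The number of total responses, errors, repetitions, and stops will be recorded". Outcome measures says that "cognition (number of correct, incorrect and total responses) will be analyzed, and compared with performance in the single-task modality", expressed as dual-task cost. This analysis is described as additional to the primary outcome.

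Two statements of purpose stand side by side. The Introduction's hypothesis is that adding cognitive training "can improve gait speed performance under dual-task conditions by, at least 0.08 m/seg". The Discussion describes the trial as investigating "whether dual-task performance, including gait and cognitive parameters, can be improved by specific dual-task training". The Introduction also notes that attention is limited and that "The dual-task cost can be accounted for in both the physical and the cognitive domains".

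**The concern.** With limited attention and free prioritisation, a resident can walk faster for two reasons: both tasks have become easier to combine, or more attention now goes to walking and less to answering. The primary score is the same in either case. The task-integration model described in the Introduction concerns the first reason only.

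The two programmes could plausibly shift this balance differently. Only the dual-task arm practises answering an instructor during exercise, with tasks of the same kind as the test tasks (semantic fluency, counting, inhibition). If that arm keeps answering and the comparator answers less, a real gain could be masked. If the shift runs the other way, a speed difference could overstate the gain.

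What is at stake is the wording of the conclusion. The response data could settle which reading applies, but only if they are analysed on a scale that does not itself move with walking time.

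**Working it through.** The plan gives no figure on this point to reproduce. It states neither the slowing caused by the cognitive task nor a response rate, and the sample size is not at issue here.

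**1. What the primary test can see.** Input: speed = 9 m / time (Outcome measures). The test uses speed alone. A between-arm difference of 0.08 m/s therefore has the same chance of reaching p < .05 whether it comes from better integration or from attention moved to walking. The speed result cannot separate the two.

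**2. What the planned response counts can see.** Let a resident give correct answers at rate r per second and walk at speed v. The count on the walk is N = r × 9/v. If speed rises by the target of 0.08 m/s and r stays the same, the relative change in N is v/(v + 0.08) − 1 = −0.08/(v + 0.08). The starting speeds below are assumptions; the article gives none.

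| Starting speed (m/s) | Time before (s) | Time after (s) | Change in count at unchanged rate |
|---|---|---|---|
| 0.5 | 18.0 | 15.5 | −0.08/0.58 = −13.8% |
| 0.6 | 15.0 | 13.2 | −0.08/0.68 = −11.8% |
| 0.7 | 12.9 | 11.5 | −0.08/0.78 = −10.3% |
| 0.8 | 11.3 | 10.2 | −0.08/0.88 = −9.1% |
| 0.9 | 10.0 | 9.2 | −0.08/0.98 = −8.2% |

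A resident with a pure gain in walking and no loss of cognitive output would thus give 8% to 14% fewer answers, which looks like a trade-off. Conversely, an unchanged count at 0.6 m/s rising to 0.68 m/s means that the response rate went up by 0.68/0.60 − 1 = 13%. The count mixes effort with walking time. The same dependence carries into cognitive dual-task cost when that cost is built on counts, unless the single-task test is matched to the walking time.

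**3. Percent correct instead of counts.** The Introduction names percent correct as an alternative for cognitive cost. It does not depend on walking time, but on a self-paced task (fluency, backward counting) a resident who answers half as often and is always right still scores 100%. It suits the Go/no-go task, where the evaluator sets the pace, provided unanswered cues count as not correct.

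**4. How large a shift would matter (illustration only).** Assume that the cognitive task slows walking by 0.10, 0.20 or 0.30 m/s.
- The 0.08 m/s target is then 0.08/0.10 = 80%, 0.08/0.20 = 40% or 0.08/0.30 = 27% of that slowing.
- Assume further that 20 percentage points more residents in one arm stop answering and return fully to single-task speed. The arm difference is then 0.20 × 0.10 to 0.20 × 0.30 = 0.02 to 0.06 m/s, or 25% to 75% of the target.

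Both assumptions come from outside the article. They give a scale, not a probability.

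**The case against.** The strongest reply is that nothing is broken. The hypothesis is about dual-task gait speed, the primary outcome measures exactly that, and the sample size is based on it. One primary outcome need not answer every aim named in a Discussion. Leaving prioritisation free is a legitimate test design. Cognitive responses are recorded and analysed, and detailed rules of interpretation are often left to a fuller plan. Most of this stands.

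A reader might go further and infer that the primary comparison is biased, or that an arm can win by dropping the cognitive task. The documents do not support that, for four reasons:
- Residents are told to perform the task while walking. Giving no priority is not permission to stop.
- Both randomised arms take the same test, and data gatherers are blinded, so a difference between arms remains an effect of the programme. Only its meaning is open.
- The most natural mechanism, in which the trained arm keeps answering, works against the trial's hypothesis.
- No passage gives the size or frequency of a shift.

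What the reply does not meet is narrower. The Discussion's aim covers both domains, and the analysis that would check the cognitive side is stated in numbers of responses over a fixed distance. That choice is written in the article, and it weakens the check on which the reply relies.

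**Conclusion.** The point holds as one of interpretation and of outcome scale. The primary outcome is valid for its stated hypothesis. A significant result supports faster gait under dual-task conditions. It does not alone support improved dual-task performance across gait and cognition, and counts on the 9 m walk would not cleanly show whether cognition paid for the speed.

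The size that can be stated is the artefact in the counts: a fall of 8% to 14% for a 0.08 m/s gain, given assumed starting speeds of 0.9 to 0.5 m/s and an unchanged response rate. The 27% to 80% and 0.02 to 0.06 m/s figures depend on assumed slowing and, for the latter, assumed excess stopping. They are not evidence that bias is likely. This is an inexpensive improvement, not an error that invalidates the design.

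**What to change.** Keep the primary outcome, the test instruction and the primary test. In Outcome measures:

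1. Name as a key secondary outcome the between-arm difference, with 95% CI, in correct responses per second on the same dual-task walks. For the evaluator-cued Go/no-go task use percent correct, with unanswered cues counted as not correct. Report it beside the speed difference, separately for each cognitive task.
2. Tabulate, by arm and visit, the walks in which responding stopped.
3. State that a significant speed difference alone supports faster gait under dual-task conditions, and that any wording about improved overall dual-task performance must rest on both results.

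A formal no-loss criterion is not proposed. It would need a margin and an SD for the cognitive score, and the article gives neither.

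The cost is protocol wording and two tables. Correct responses and walking time are already collected. The article does not list the number of Go/no-go cues, nor say whether the recorded stops are in walking or in responding; if these are not on the test form, they need one extra entry each. The downside for the investigators is a narrower claim if the response rate falls.
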